**Methods:**

This is a prospective observational multicenter mixed study. Relatives of adult patients with a neoplasia expected to be hospitalized more than 72 h in a palliative care unit for end-of-life issues will be included within 48 h after patient admission. End-of-life issues are defined by the physician at patient admission. Relatives who are not able to have a phone call at 6-months are excluded. The primary outcome is the incidence of prolonged grief reaction defined by an ICG (Inventory Complicate Grief) > 25 (0 best-76 worst) at 6 months after patient’ death. Prespecified secondary outcomes are the risk factors of prolonged grief, anxiety and depression symptoms between day 3 and day 5 and at 6 months after patients’ death based on an Hospital Anxiety and Depression score (range 0–42) > 8 for each subscale (minimal clinically important difference: 2.5), post-traumatic stress disorder symptoms 6 months after patient’ death based on the Impact of Events Scale questionnaire (0 best-88 worst) score > 22, experience of relatives during palliative care based on the Fami-Life questionnaire, specifically built for the study. Between 6 and 12 months after the patient’s death, a phone interview with relatives with prolonged grief reactions will be planned by a psychologist to understand the complex system of grief. It will be analyzed with the Interpretative Phenomenological Analysis. We planned to enroll 500 patients and their close relatives assuming a 25% prolonged grief rate and a 6-month follow-up available in 60% of relatives.

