Risk factors of prolonged grief disorders were reported in numerous studies [5–9]. Conflicts between relatives and health-care workers, poor communication and incomplete information during the palliative care stay [9], relatives characteristic’s: age, female gender [8, 10], pessimistic or anxious personality trait [10], financial issues [6], close relation-ship with the deceased patient [7, 10], absence of religiosity [10], and specific social context and family dynamics [11, 12] were reported as risk factors for prolonged grief. Numerous studies worldwide have evaluated post-loss emotional consequences. At 6 and 13 months, at least one psychological consequence was identified in 35.6 and 28.9%, respectively [13]. In Korea, anxiety and depression symptoms were reported for 58 and 57%, respectively [14]. In Australia, PTSD symptoms was diagnosed in 27.6 and 18.3%, respectively [13]. In Portugal, PGD was diagnosed in 28.6 and 15.6%, respectively [15]. In France, numerous studies are focused on population faced to end-of-life situations for intensive care patients [9, 16, 17]. Surprisingly, very few studies are available on relatives of palliative care patients. A French study reported depression in 25% of cancer patient’s spouses after a loss [18].

No data exists on the psychological experience of relatives having a relative hospitalized in palliative care or the incidence of prolonged grief in France. No specific recommendations are available for supporting grieving relatives.

Therefore, the focus of the study will be on prolonged grief reactions in relatives around 6 months after patient’s death in palliative care units. The methodology includes quantitative and qualitative data to better understand the complex, unique and intimate phenomena of grief and to identify needs for support.

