#### Data collection

##### Center characteristics

All data will be collected on an e-CRF built by the ICUREsearch company (Contract Research Organization). Data will be on center, patients and relatives. Palliative care unit characteristics are the following: hospital type (university, community, or private hospital) number of palliative care beds, number of senior physicians and fellows, physician-to-patient ratio, nurse-to-patient ratio (day and night), presence of a waiting room and relative room, availability of a psychologist, physiotherapist, social worker, occupational and music therapist, biographer; availability of interpret or religious services; availability of a dedicated nurse for relative meetings, of volunteers, of speaking group for relatives; time intervals allowed for visit; organization of different meetings (admission, weekly, death period), delivery of an information leaflet at admission and after death, delivery of a children leaflet, delivery of a condolence letter, bereavement follow-up process, availability of a 24-h visitation policy, age for children visitation, possibility for a pet to visit the patient, availability of staying during the night (bed in the patient ‘room, dedicated room, other), and participation in patient care.

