### Statistical analysis plan

Patient, relatives and center-variables are reported as numbers (percentage) for qualitative data and medians (Q1–Q3) for quantitative data. For continuous variables, we perform tests of logit linearity and transformation if necessary. Strategy of imputation of missing values will be adapted according to the pattern of missing values. The missing data will be considered by a simple imputation method in case of low frequency (less than 2%) or by multiple imputation if the frequency is higher. Variables with more than 30% missing data will not be included in the analysis. No imputations will be performed for patient outcomes. The primary outcome is the incidence of relatives with an IGC score > 25. The incidence rate will be defined by the ratio between the number of persons who have a prolonged grief on the number of person-time in the study. A 95% Wald confidence interval will be computed for the incidence rate.

To assess the risk factors for prolonged grief in patients’ relatives, multivariable hierarchical logistic regression model will be performed, with a random effect on the center. An univariable analysis will be first performed to select the variables associated to the outcome with a *p*-value threshold of 0.2 to account for the main confounding factors. The relative effect can be considered either as a random effect or a fixed effect in the model. We will then perform multivariable logistic or negative-binomial models for the modification of anxiety, depression and PTSD scores for the secondary criteria. To account for the rate of lost-to-follow-up within the relatives, a weighting on the inverse probability of censoring weight (IPCW) will be performed. All statistical analyses were performed using the SAS software (SAS 9.4, SAS Institute, Cary, NC). A *p* value < 0.05 will be considered significant.

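### Choosing covariates by univariable p < 0.2 can drop real confounders, and testing a large candidate pool at p < 0.05 with few events makes at least one false risk factor likely

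*Protocol article*

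**What the plan says.** The section Statistical analysis plan of the protocol article sets out a two-step rule. For step one: "An univariable analysis will be first performed to select the variables associated to the outcome with a" cut-off on the univariable p. The article describes this cut-off and its purpose as a "threshold of 0.2 to account for the main confounding factors". For step two, a "multivariable hierarchical logistic regression model will be performed, with a random effect on the center". A p "value < 0.05 will be considered significant".

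The secondary-outcome text says that risk factors will be explored through centre, patient and family characteristics. Those are the three lists under Data collection. The centre list is the longest and runs to items such as "presence of a waiting room and relative room, availability of a psychologist, physiotherapist, social worker, occupational and music therapist, biographer".

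The only limit stated on the pool is that variables with more than 30% missing values are left out. The article states no covariates kept regardless of p, no cap on model size, no shrinkage and no multiplicity adjustment. Yet its Background begins one paragraph with "Risk factors of prolonged grief disorders were reported in numerous studies" and goes on to name several.

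**The concern.** The stated purpose of the screen is control of confounding, and the screen is not suited to it. A variable confounds through its relation to both the exposure and the outcome. When it is correlated with another factor whose effect runs the other way, its crude association with the outcome shrinks. It may then miss p < 0.2 even though adjustment for it matters.

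Selection and testing also use the same data, and the reported p-values and intervals take no account of that. The pool of collected variables is large relative to the expected number of events, and each survivor is judged at an unadjusted 0.05.

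Risk factors are a prespecified secondary outcome, the sample size is justified by detecting them, and the Discussion hopes to help clinicians target interventions. A false factor could misdirect that effort, and an omitted confounder would distort the odds ratios that guide it.

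**Working it through.** **1. The plan's own sample size.** The article gives OR 2, alpha 0.05, power 0.80, 25% prolonged grief, 60% follow-up and 500 decedents with their relatives. Take 25% as the risk in the unexposed. The exposed odds are 2 x 0.25/0.75 = 0.667, so the exposed risk is 40%. The pooled two-proportion formula (two-sided, no continuity correction) is

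n per group = [1.960 x sqrt(2 x 0.325 x 0.675) + 0.842 x sqrt(0.25 x 0.75 + 0.40 x 0.60)]² / 0.15² = 152.

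That is 304 relatives in total, and 304/0.60 = 507, close to 500. The match needs an assumed 50% exposure and covers one unadjusted factor. At 20% exposure, power with 300 relatives is about 0.61 to 0.63.

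**2. Expected events.** The abstract says "We planned to enroll 500 patients and their close relatives", "assuming a 25% prolonged grief rate and a 6-month follow-up available in 60% of relatives".
- One relative per patient: 500 x 0.60 x 0.25 = 75 events.
- Two per patient (an assumption; the article allows several but gives no average): 1000 x 0.60 x 0.25 = 150 events.

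**3. Candidates.** Itemising the three Data collection lists gives about 34 centre, 14 patient and 11 relative variables, 59 in all. Grouping similar items gives about 50. At 55 there are 75/55 = 1.4 to 150/55 = 2.7 events per candidate.

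**4. False risk factors.** The two-step rule was simulated with binary candidates, incidence near 25%, 300 to 500 studies per scenario and ordinary logistic regression without a centre effect. True factors have OR 2.

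| Scenario | False factors per study | Studies with at least one | True factors lost at screen |
|---|---|---|---|
| 300 relatives, 20 null, independent | 1.1 | 61-65% (two runs) | - |
| 300 relatives, 55 null, independent | 2.9 | 93% | - |
| 300 relatives, 55 of which 5 true | 2.5 | 92% | 15% |
| 300 relatives, 40 of which 5 true | 1.9 | 85% | 14% |
| 300 relatives, 55 of which 5 true, latent correlation 0.1 | 1.7 | 78% | 7% |
| 600 relatives, 55 of which 5 true | 2.3 | 91% | 2% |

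A further run of the 55-null scenario gave 96%.

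**5. Where the false factors come from.** In the null scenarios the rate per candidate is 2.9/55 = 5.3% and 1.06/20 = 5.3%, which is essentially nominal. Unadjusted testing alone predicts 1 - 0.95^55 = 94% and 1 - 0.95^20 = 64%, which agrees with the table. A full 55-variable model with no screen gave more false factors: about 4.3 per study at 300 relatives.

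**6. Dropped confounders.** Setting: 300 relatives, an exposure with OR 2, a confounder correlated -0.5 with it on the latent scale, and 1000 runs. Odds ratios are averages (on the log scale) over all runs.

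| Confounder OR | Fails p < 0.2 | Exposure OR, adjusted | Exposure OR, confounder omitted |
|---|---|---|---|
| 1.5 | 68% | 1.99 | 1.73 |
| 1.8 | 46% | 1.99 | 1.62 |

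With zero correlation and OR 1.5 the variable still failed in 40% of runs, but omitting it hardly mattered (1.98 against 1.99). The harm therefore depends on correlation between the factors.

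**The case against.** The strongest reply is that the screen is blamed for what multiplicity does. A reader might infer from the tables that the p < 0.2 step creates the false factors, or that it raises type I error from 5% to about 26%. Neither follows. The 26% is the rate among null variables that have already passed the screen (about 0.05/0.20 = 25%). Over all candidates the rule stays near 5% per variable, and a full model without the screen does worse. This objection stands, and it limits the point to multiplicity with few events plus the separate problem of masked confounders.

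Other replies also have force:
- **Candidate pool.** The article lists what is collected and does not say that every item will be screened. The exact candidate list is something an article may leave to a fuller plan. The 55 is therefore conditional, and the 20-candidate figure is the fairer lower case.
- **Near-certainty.** A reader might call a false finding close to certain. That holds only for a large independent pool; mild correlation brings it to 78%. The simulations also omit the centre random effect. About 34 candidates vary only between centres, so their information is limited by the number of centres.
- **Events.** Seventy-five assumes one relative per patient. At 150, loss of true OR-2 factors is small, though false factors remain as likely. Clustering within families and the restriction of calls to deaths in the unit reduce the information.
- **Inflated odds ratios.** A reader might expect published estimates to be exaggerated. That was not calculated and is not claimed.
- **Importance.** The primary outcome, incidence, is untouched. The risk-factor aim is secondary and described as exploration.

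None of this rescues the screen as a device for confounding control. The rule and its purpose are both fixed in the article, and covariates forced in regardless of p would contradict that text.

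**Conclusion.** The point holds in two parts, and the plan should be changed.

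First, the screen does not do what it is said to do. Under the assumed correlation of -0.5 and confounder odds ratios of 1.5 to 1.8, it discards the confounder in 46% to 68% of runs, and an exposure odds ratio of about 2.0 is then estimated at about 1.6 to 1.7. The sizes are illustrative, but the mechanism is general.

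Second, with no multiplicity control stated and p-values that ignore the selection, at least one false risk factor is likely. The probability is about 60-65% with 20 independent null candidates, about 78% with 55 mildly correlated candidates and about 93% with 55 independent null ones. This rests on how many collected variables are really candidates and on independence between relatives. It stems mainly from many unadjusted tests with few events, not from the screen.

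The finding concerns the secondary risk-factor analysis only.

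**What to change.** Replace the p < 0.2 screen with a short covariate set fixed before the outcome data are examined and entered whatever its univariable p. Size it at about 1 df per 10 expected events: 75/10 gives about 7 df at one relative per patient. More is defensible only if several relatives per patient are followed, after allowing for family clustering. Multi-category variables count for all their df.

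Start from factors that the Background names and the study collects: the relative's age and sex (assuming these are within the demographic data) and relationship to the patient. Add others only with a stated reason. One candidate is the HADS at day 3 to 5, as a measure of early anxiety. Surrogate status and educational level are collected, but the Background does not name them as risk factors, so they would need their own justification.

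Label all other patient, relative and centre variables exploratory. Analyse them with false-discovery-rate control or a penalised model. Keep the centre random effect. Removing the screen while leaving every variable in one unadjusted model would not be an improvement.

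The cost is a change of analysis wording and a short list, with no new data. The downside is that fewer factors can be headlined as independent risk factors.

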#### Recruitment of patients and relatives

##### Inclusion criteria

All the inclusion criteria must be fullfilled within 48 h after patient admission:

Patients with a neoplasia should be hospitalized more than 72 h for end-of-life issues. End of life issues are assessed after the first evaluation by the palliative care physician.

Relatives are susceptible to visit the patient during their stay. Relatives are defined as spouse, partner, children, siblings, parents and cousins and any relatives with a strong attachment link. The study will be proposed to relatives present during the first meeting and within 48 h after patient admission. All relatives present can be included because the patient’s death affects the entire group of relatives and not a single individual.

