### Sample size justification

Prolonged grief reactions were reported in 24.4% [10] at 8 months, and 25.4% [31], 28.6% [15], 30% [32], and 40% [33] at 6 months. We anticipated an incidence of prolonged grief of 25% 6 months after patient death. Horowitz et al reported that the frequency of grief symptoms declined within 6 to 12 months after the bereavement [34]. Grief reactions decreased as a function of time from death with a steepest decrease from the first month to the sixth month after death, and without any significant decrease from 6 months to 13 months [33, 35]. For the current study, we selected a time period of 6 months after the death. According to the medical knowledge, longitudinal studies of relatives at 6 months usually report a participation rate around 60%. To detect the risk factors associated with a prolonged grief with an odd ratio of 2, an alpha risk of 0.05 and a power of 0.80, we anticipate that 500 decedents and their relatives are necessary (assuming the independence of prolonged grief in the relatives of the same family).

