## Discussion

This study will depict the grieving process of relatives after patient ‘s death in palliative care in France. According to the World Health Organization definition of palliative care, providing support for the relatives during their grieving process is an inherent part of palliative care services [36]. Currently, there is no consensus to which type and amount of support is indicated to meet the demand of the WHO definition of bereavement support in palliative care [37]. There are hardly substantial pieces of knowledge on how bereavement of relatives of palliative care patients is handled. The need for support in the bereavement period was poorly predicted by the healthcare clinicians [33]. Having baseline data of the incidence rate of prolonged grief and other psychological consequences, of risk factors of relative’s prolonged grief, and better knowledge of the management of end-of-life issues in palliative care units will increase our knowledges on the grieving process. Currently, palliative care team have different strategies for managing grieving relatives. No scientific data are available on these practices, and there are no national guidelines with a sufficient high grade of proofs.

The strengths of this study will be the high number of relatives included, and the multicenter design with the recruitment of patients from a large set of centers with patient’s characteristics consistent with those of patients usually admitted in palliative care in France, which will ensure that results could be generalized. The mixed design will enable to approach how relatives experience the period of bereavement and to help healthcare clinicians in targeting interventions to decrease bereaved relative’s burden.

This study will have several limitations. First, the exploration of psychological consequences will focus on patients with neoplasia, who do not represent all the case-mix of patients admitted in palliative cares. Second, evaluation will be performed at only one time-point, which is insufficient to describe the evolution of the grieving process. We choose one point to limit the rate of lost-to-follow-up among relatives. Third, the centers are all in France, and the study results might not be generalized to other countries.

Our study is part of a scientific approach to the management of grief in palliative care to build a scientifically valid management program.

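### Relatives of one patient are analysed together, but the plan states no family-clustered variance for the primary interval and no firm family term in the risk-factor model

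*Protocol article*

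**What the plan says.** All references are to the protocol article.

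- *Inclusion criteria*: "All relatives present can be included because the patient’s death affects the entire group of relatives and not a single individual". No cap on relatives per patient is given.
- *Statistical analysis plan*, primary outcome: "The primary outcome is the incidence of relatives with an IGC score > 25". The unit is the relative. On precision: "A 95% Wald confidence interval will be computed for the incidence rate".
- *Statistical analysis plan*, risk factors: a "multivariable hierarchical logistic regression model will be performed, with a random effect on the center". Further on: "The relative effect can be considered either as a random effect or a fixed effect in the model".
- *Sample size justification*: 500 decedents and their relatives, for an odds ratio of 2, alpha 0.05 and power 0.80, "assuming the independence of prolonged grief in the relatives of the same family".
- *Measure of the prespecified secondary outcomes*: candidate risk factors are taken at unit, patient and relative level.
- *Table 1* schedules the ICG once, at 6 months, and the HADS twice, at day 3 to 5 and at 6 months.

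No patient or family random effect, GEE or family-clustered variance is named anywhere in the article.

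**The concern.** Relatives are nested in patients, and patients in centers. The reason given for enrolling several relatives, a death that acts on the whole group, is also a reason to expect their ICG outcomes to be positively correlated. The sample size section assumes the opposite, and the analysis section names only the outer level of the nesting. A center effect absorbs correlation common to everyone in a unit. It does not absorb the extra correlation between relatives of the same patient.

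Two results are exposed: the precision of the primary incidence, and tests of risk factors that all relatives of a patient share, such as diagnosis, continuous sedation, length of stay and unit practices. The second is the aim on which the sample size was based.

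**Working it through.** **1. The plan's own figure.** An odds ratio of 2 on 25% gives odds 2 × 0.25/0.75 = 0.667, so 40%. Comparing 25% with 40% (two-sided 0.05, power 0.80, equal groups, no continuity correction) needs 152 per group, or 304 relatives with an outcome. With 60% participation, 304/0.60 = 507, close to the stated 500. Two-sided testing, 50% exposure and 25% as the rate in the unexposed are my assumptions. The match also needs independent relatives. With 300 relatives the power is 79.5%.

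**2. What 'relative effect' could mean.**

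- *One effect per relative.* Each relative has one binary ICG outcome; the Discussion concedes that "evaluation will be performed at only one time-point, which is insufficient to describe the evolution of the grieving process". A fixed effect then has one parameter per observation, and a random intercept has no replication within relatives to identify its variance.
- *Family, fixed.* Patient- and center-level factors are constant within a family and drop out. Families with one relative, or with relatives who all have the same outcome, carry no information. At 25% prevalence under independence, 1 − 2 × 0.25 × 0.75 = 62.5% of pairs are concordant. Positive correlation raises this: at ICC 0.26, 1 − 0.375 × 0.74 = 72%.
- *Family, random.* Estimable and suitable, but neither defined nor committed to.
- *Relationship type* (spouse, child and so on). An ordinary covariate, which does not deal with clustering.

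**3. Primary interval.** I treat the incidence as a proportion of 25%. With m responding relatives per patient and intraclass correlation ICC, the design effect is DE = 1 + (m − 1) × ICC. The true standard error is √DE times the naive one, and a nominal 95% interval covers 2Φ(1.96/√DE) − 1. For 300 relatives the naive half-width is 1.96 × √(0.1875/300) = 4.9 points. Both m and ICC are assumed; the document gives neither.

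| m | ICC | DE | SE ratio | true half-width (points) | coverage |
|---|---|---|---|---|---|
| 1 | any | 1.00 | 1.00 | 4.9 | 95.0% |
| 1.5 | 0.1 | 1.05 | 1.02 | 5.0 | 94.4% |
| 2 | 0.2 | 1.20 | 1.10 | 5.4 | 92.6% |
| 2 | 0.3 | 1.30 | 1.14 | 5.6 | 91.4% |
| 3 | 0.3 | 1.60 | 1.26 | 6.2 | 87.9% |

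Coverage depends on DE, not on the number of relatives. If 300 patients each had m responding relatives, the half-width would be 3.5 points naive against 3.8 true (m=2, ICC 0.2, 600 relatives), or 2.8 against 3.6 (m=3, ICC 0.3, 900 relatives). The shortfall in coverage would be the same.

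**4. Risk-factor tests.** Simulated logistic regressions with 300 relatives, about 25% prevalence, a random family intercept, a null factor with 50% exposure and 1,500 studies per setting (Monte Carlo error √(0.05 × 0.95/1500) = 0.6 points). No center effect was simulated.

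| m | ICC (approx.) | shared factor, no family term | shared factor, family-cluster-robust | factor varying within family, no family term |
|---|---|---|---|---|
| 2 | 0.14 | 7.2% | 5.3% | 5.4% |
| 2 | 0.32 | 8.7% | 4.6% | 4.5% |
| 3 | 0.14 | 7.8% | 4.5% | 5.3% |
| 3 | 0.32 | 13.9% | 5.7% | 4.9% |

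**5. Power for a shared factor.** If the total is 300 relatives with an outcome, power falls from 79.5% to 71.9% (m=2, ICC 0.2) or 59.3% (m=3, ICC 0.3). If instead 300 patients each supply m relatives, the effective number is 300m/DE, for example 600/1.20 = 500, and power is not reduced.

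**The case against.** The strongest reply is that the plan may already contain the remedy. The sentence on the 'relative effect' stands in a paragraph on a hierarchical model, and it may mean the group of relatives around one patient, with a random effect as one option. In addition, 'Wald' fixes the form of an interval, not its variance estimator, and a condensed article may leave the estimator to a fuller plan. This stands in part: a reader might infer that the plan excludes any family term, and the text does not support that. But the article does specify the cluster level, the interval and a choice between random and fixed. It states independence within families for the sample size, and nowhere names a variance that allows for families. An undefined effect with an unsuitable option left open is not a commitment, and even a random family effect in the risk-factor model would leave the primary interval as it is.

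A reader might also infer that all standard errors will be too small, or that the damage is large. Neither follows. Factors that vary independently between relatives of one patient kept a type I error of 4.5 to 5.4%; age, sex or education may come close to this. Corner values such as m=3 with ICC 0.5 (DE 2.0, coverage 83.4%) are possible, but nothing in the document points to them, and 60% participation pulls the number of responders per patient down. Nor does the document show that the study is underpowered, since that depends on whether extra relatives come on top of one per decedent.

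**Conclusion.** The concern holds in a limited form. As written, the plan gives too narrow a primary interval, and too many false positives for family-shared factors, whenever more than one relative per patient responds and their outcomes are positively correlated. The sentence on the 'relative effect' does not reliably prevent this, because only one of its readings works and the plan does not choose it.

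The size cannot be fixed from the document. It is nil at one relative per patient and slight at m=1.5 with ICC 0.1. Over the assumed range up to m=3 with ICC 0.3, coverage falls to about 88%. Type I error for shared factors is about 7 to 14% at m=2 to 3 and ICC 0.14 to 0.32. The direction is certain under positive correlation, which the protocol's own reason for enrolling several relatives makes likely. It should be settled before the analysis.

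**What to change.** - Replace the 'relative effect' sentence with a random intercept for the patient (family), nested in the random center effect, and delete the fixed-effect option. If relationship type was meant, keep it as an ordinary covariate and say so.
- Compute the primary 95% interval with a variance clustered on the patient, or with a bootstrap that resamples patients.
- Use the same family clustering in the IES-R and HADS models. If both HADS time points are modelled jointly, add a random effect for the relative, which is then identifiable.
- In *Sample size justification*, state that the power holds as calculated only under independence, or show it with a design effect over a range of m and ICC. Enrolment need not change.

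The cost is analysis wording and one added sentence on power. Intervals become modestly wider, and nothing is lost if most patients turn out to have a single responding relative.
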